## Abstract

**Abstract:**

**Introduction:**

Stroke is a leading cause of long-term disability, yet recovery trajectories are highly heterogeneous and difficult to predict at the individual level. Standardised clinical assessments primarily capture task accomplishment under controlled conditions but may overlook changes in movement quality, including the distinction between compensatory strategies and behavioural restitution. Additionally, they provide limited insight into the postural control processes that underlie functional task performance. Recent consensus initiatives emphasised the need for sensitive, functionally relevant measures of balance and mobility after stroke. Integrating routine clinical assessments with a sensor-based approach during functional tasks offers new opportunities to characterise recovery more precisely and to map longitudinal trajectories of poststroke change. Within the European Union-funded TARGET project, the FOSTER study aims to generate multimodal data to support data-driven, individualised prognostic models, so-called virtual twins, for personalised rehabilitation.

**Methods and analysis:**

FOSTER is a prospective, single-centre observational cohort study at Rehabilitation Hospital Inkendaal (Belgium). We aim to include 100 adults within 8 weeks poststroke, assessed at three to five time points, including an entry assessment after admission and follow-up assessments within predefined windows at approximately 5, 8, 12 and 24 weeks poststroke. The protocol combines synchronised sensor-based measurements during functional tasks (seated reaching, standing reaching and gait initiation) obtained during an exergame, with standardised clinical tests and patient-reported outcome measures (PROMs). Sensors include surface electromyography, inertial measurement units, force plates and markerless motion capture. Sensor-based measurements target movement quality, and anticipatory and reactive postural control during self-initiated functional tasks. Derived outcomes will capture kinetic, kinematic and neuromuscular features of movement strategies, including temporal and asymmetry characteristics. In addition, in-task performance metrics, real-world activity monitoring through accelerometry, standardised clinical assessments and PROMs will be collected to provide a comprehensive, multimodal characterisation of recovery. Linear mixed-effects models will characterise longitudinal trajectories and relationships between clinical and sensor-derived measures.

**Ethics and dissemination:**

The FOSTER study was approved by the Ethics Committee of Rehabilitation Hospital Inkendaal (B.U.N. 2024-TEE-002). Participants will be included after providing informed consent. Data are pseudonymised and stored on a General Data Protection Regulation-compliant platform. Findings will be disseminated through peer-reviewed publications, conferences and within the TARGET consortium.

**Trial registration number:**

NCT06806761.

STRENGTHS AND LIMITATIONS OF THIS STUDYProspective, longitudinal protocol with three to five predefined time points in the first 6 months poststroke.Task-specific, game-based assessments designed to elicit natural movement while maintaining standardisation across sessions.Integration of multiple sensor modalities (surface electromyography, inertial measurement units, force plates, markerless motion capture) enables objective quantification of postural control and movement quality.Single-centre, observational design may limit generalisability and precludes causal inference.Repeated multisensor assessments may increase participant burden and missing data, particularly among more impaired individuals.

## Introduction

 Stroke remains one of the leading causes of long-term disability worldwide, with substantial societal and individual burdens. In Europe alone, over one million people experience a stroke annually. Stroke is typically accompanied by interacting deficits like muscle weakness and impaired postural control, often resulting in persistent limitations in mobility and reduced functional independence.^1–3^ Recovery of mobility largely depends on both the restoration of lower extremity function and the ability to regain adequate postural control.^4
5^ Despite well-established evidence-based rehabilitation guidelines, recovery trajectories remain highly heterogeneous and difficult to predict at the individual level, posing a major clinical challenge.^6
7^ Recent advances in artificial intelligence have been proposed as a promising avenue to address this challenge by integrating heterogeneous clinical and physiological data to support personalised prediction and management strategies across the atrial fibrillation (AF-)stroke continuum.^8^

Standardised clinical assessments, such as the Fugl-Meyer assessment (FMA), Berg Balance Scale (BBS) or Functional Independence Measure (FIM), play a vital role in monitoring rehabilitation progress and guiding clinical decision-making.^4
9^ These instruments provide structured evaluations of motor impairment, balance and functional independence and are widely implemented in both research and clinical practice.^4^ Most existing prediction models for motor recovery, including the Predict Recovery Potential 2 (PREP2) algorithm for the upper limb^10^ and the TWIST algorithms for ambulation,^11^ are largely dependent on baseline demographic characteristics and clinical assessment scores, making their prognostic value dependent on the scope and sensitivity of these measures. While valuable for early stratification and outcome monitoring, clinical assessments primarily evaluate task accomplishment under controlled conditions.^12–19^

Beyond task accomplishment, a limitation of standardised clinical assessments is that they provide limited insight into movement quality, as they are unable to distinguish behavioural restitution, that is, re-acquisition of prestroke movement patterns, from compensatory strategies, that is, substitution for, or circumvention of, impaired functions.^20
21^ Additionally, they provide limited insight into the mechanisms underlying postural control, which involves multisensory integration and the interaction between anticipatory (feedforward) and reactive (feedback) processes.^22–24^ Anticipatory (feedforward) postural control prepares the body for self-generated disturbances, whereas reactive (feedback) control restores stability following movement execution.^25–27^ Together, this highlights the need for complementary assessment approaches with greater sensitivity to underlying movement quality, as emphasised by recent international consensus initiatives on poststroke outcome measurement.^4
9
28–30^

Sensor technologies, especially wearable ones, offer promising opportunities to address these limitations by enabling objective, fine-grained and even continuous measurement of movement and postural control during functional tasks.^31–34^ Depending on the modality, sensors such as force plates, surface electromyography (sEMG), and inertial measurement units (IMUs) provide complementary information on kinetics (eg, asymmetric weight distribution), muscle activation patterns (eg, delayed muscle activation) and kinematics (eg, excessive trunk displacement). By quantifying these dimensions, sensor-based assessments enable more detailed characterisation of underlying movement quality and compensatory strategies. Importantly, especially wearable sensors facilitate measurement within functionally relevant contexts while maintaining standardisation and reproducibility, thereby helping bridge the gap between standardised clinical testing and functionally representative movement assessment.^35
36^

Although previous studies have demonstrated the potential of (wearable) sensor technologies to capture impairments in underlying movement quality and postural control after stroke,^34
37–40^ most investigations have been cross-sectional or confined to controlled laboratory settings.^41–43^ As a result, they provide only a glance at recovery and do not capture the temporal dynamics that characterise functional improvement. This limitation is particularly relevant given that poststroke recovery follows a non-linear trajectory, typically characterised by early gains followed by periods of plateau and consolidation.^44
45^ Capturing such dynamic changes requires longitudinal assessments that extend into clinically relevant phases of recovery.

To address this, the FOSTER (‘Follow-up study of stroke patients using sensors for the evaluation of functional ability and compensatory movements’) study was initiated within the EU-funded TARGET project (‘Health virtual twins for the personalised management of stroke related to atrial fibrillation’; grant agreement: 101136244).^46
47^ TARGET aims to improve outcomes after AF-related stroke through the development of individualised ‘health virtual twin’ models, that is, AI-driven simulations designed to support personalised clinical decision-making across the care pathway, from prevention and acute management to rehabilitation and long-term follow-up.^46
47^ Complementing this objective, FOSTER broadens the scope to poststroke recovery across all aetiologies, with prospective follow-up up to 6 months poststroke.

The overarching aim of the FOSTER clinical study is to collect longitudinal data on postural control and functional activity during the subacute phase after stroke. A multimodal assessment protocol will be applied that combines sensor-based assessments during functional activities, allowing the distinction between behavioural restitution and compensatory mechanisms, with standard clinical outcome measures. The primary objective is to characterise longitudinal change in sensor-derived postural control and movement quality. This primary outcome construct is operationalised across four equally ranked outcome domains: postural control, weight distribution, movement coordination and neuromuscular activity. Secondary objectives are to characterise longitudinal change in task-performance measures, daily activity, clinical outcomes and patient-reported outcome measures (PROMs), and to examine associations between sensor-derived metrics of movement quality and clinical outcome measures.

## Methods and analysis

### Project status

Patient recruitment and assessments started in January 2025 at Rehabilitation Hospital Inkendaal. By July 2026, halfway through the planned 36-month data collection period, 56 participants had been included and both recruitment and follow-up assessments were ongoing.

### Study design and setting

FOSTER is a prospective, single-centre observational cohort study conducted at the Rehabilitation Hospital Inkendaal, a specialised rehabilitation hospital located in Vlezenbeek, Belgium. The rehabilitation hospital includes two subacute neurological rehabilitation units with a total capacity of 86 beds, providing a structured setting for standardised interdisciplinary follow-up after stroke. Rehabilitation is highly individualised and delivered according to standardised care pathways, integrating physiotherapy, occupational therapy, speech and language therapy and medical follow-up tailored to each patient’s needs.

Patients are referred to Rehabilitation Hospital Inkendaal for intensive rehabilitation following acute care in a primary hospital. The study was designed to fit within the existing care trajectory for stroke rehabilitation, ensuring clinical feasibility while enabling structured data acquisition for scientific analysis. Participants are enrolled during their inpatient stay and followed up longitudinally throughout the rehabilitation process.

The study was developed in accordance with the STROBE (Strengthening the Reporting of Observational Studies in Epidemiology) guidelines for observational studies^48^ and ethical approval was granted by the local ethics committee at Rehabilitation Hospital Inkendaal (B.U.N. 2024-TEE-002).

### Patient and public involvement

Patients and members of the public were not involved in the design of the FOSTER study. However, within the wider TARGET project, a dedicated stakeholder work package has been established to ensure that the development of AI-based clinical decision-support tools reflects the needs and perspectives of end users. This programme includes co-creation activities with clinicians, patients and other stakeholders through advisory boards, focus groups, and iterative feedback processes, which inform the design and implementation of the TARGET digital tools.^46
47^

### Participants

#### Eligibility criteria

Participants are adults admitted to Rehabilitation Hospital Inkendaal for inpatient stroke rehabilitation. Recruitment is embedded in the hospital intake pathway; the multidisciplinary team flags potentially eligible patients to the research team who subsequently provides verbal and written study information and answers questions (with family present if desired). Written informed consent is obtained by the research team before any study-specific assessments.

To be eligible, adults (≥18 years old) must have experienced a supratentorial stroke (ischaemic or haemorrhagic) and be within the first 8 weeks poststroke onset at the time of inclusion. This time frame ensures that participants can complete at least three poststroke assessments (at 8, 12 and 24 weeks), in line with the study’s longitudinal design (see figure 1). The FOSTER cohort is not restricted to patients with AF-related stroke; patients are eligible irrespective of stroke aetiology, provided they meet the other eligibility criteria. Participants must also be capable of understanding and performing the study procedures that are feasible at a given assessment time point, following the advice of the treating therapist(s) and/or physician(s).

**Figure 1 F1:**
[figure not shown]
Overview of the FOSTER multimodal longitudinal assessment protocol (**A**) Assessment timeline; 3–5 assessments per participant (depending on inclusion timing) (**B**) Multimodal assessment approach; the central panel includes the in-game visual interface where the on-screen avatar, controlled by the participant’s non-paretic hand, reaches towards the target (banana). 10mWT, 10 m Walk Test; BBS, Berg Balance Scale; BL, baseline; EMG, electromyography; FAC, Functional Ambulation Category; FMA-LE, Fugl-Meyer Assessment–Lower Extremity; HADS, Hospital Anxiety and Depression Scale; IMU, inertial measurement unit; MI, Motricity Index; Mini-BEST, Mini-Balance Evaluation Systems Test; mRS, modified Rankin Scale; PROMs, Patient-Reported Outcome Measures; SF-36, 36-Item Short Form Health Survey; TIS, Trunk Impairment Scale; W, Week.

Patients are not eligible if they present with neurological or orthopaedic comorbidities unrelated to stroke that significantly impair motor function or if they have severe medical conditions that could compromise safety during the assessments. Additional exclusion criteria include major deficits in communication, memory or understanding, as well as insufficient comprehension of Dutch, French, German or English. Independent walking, standing balance or the ability to perform the exergame tasks are not required for inclusion.

### Assessment protocol

Each participant undergoes an entry visit (first study assessment) as soon as feasible after admission and informed consent. Follow-up assessments are scheduled within predefined poststroke windows at 5, 8, 12 and 24 weeks after stroke onset. As participants are eligible for inclusion within the first 8 weeks poststroke, they will complete between three and five assessments depending on their admission timing. Participants admitted later in the recovery trajectory (eg, around week 7–8 poststroke) will be scheduled at the first possible window and will subsequently be followed at the remaining scheduled windows (eg, weeks 8, 12 and 24) (figure 1).

All assessments are conducted by trained researchers, under standardised conditions in the hospital’s motion analysis lab (see further). Sessions are integrated into the rehabilitation schedule to minimise interference with therapy and last up to 120 min, including rest breaks as needed. When participants are discharged before a scheduled time point, outpatient follow-up is arranged whenever feasible.

The protocol consists of two components: (1) a series of structured, sensor-based recordings during functional activities obtained through an exergame and (2) a standardised set of clinical tests and PROMs, conducted without sensors. The clinical assessments and PROMs are completed whenever feasible, whereas the sensor-based exergame assessments are only performed when the participant is judged able to complete the respective task safely under supervision.

The sensor-based assessments are performed through an interactive game environment. The game interface (figure 1B) visualises an avatar, controlled by the participant’s non-paretic hand or a leg, who can move toward a target object. This game uses Kinect V2 markerless motion capture, placed in front of the participant, to track full-body movements in the frontal plane. Visual targets are presented on a screen to elicit controlled reaching or stepping movements. These tasks are designed to safely challenge postural control through controlled destabilisation and to elicit natural, functionally relevant movement responses.

The game embeds three core functional tasks: (1) Seated reaching: sideways reaching from a standardised seated position toward a virtual target; (2) Standing reaching: the same reaching task performed while standing; and (3) Gait initiation: initiating forward stepping in response to a visual target. Figure 1 illustrates the standing reaching condition. Reaching is always performed with the non-paretic arm, both to the paretic and non-paretic side. Stepping is performed with both the paretic and non-paretic leg as stepping leg. A minimum of 5 targets per side is collected for each functional task.

The game consists of two different levels, presented in the same order in every session. In the first level, the participant knows the location of the target in advance and waits with initiating the requested movement until a timer clock has counted down. In the second level, the target location is unknown until it appears on the screen, which is also the sign to initiate the movement.

Rehabilitation hospital Inkendaal is equipped with a motion analysis laboratory (±40 m²) including AMTI force platforms (Advanced Mechanical Technology, Watertown, Massachusetts, USA), wireless Mini Wave Infinity modules for sEMG and IMU recording (Cometa s.r.l., Bareggio (MI), Italy), four Bonita 720C video cameras (Vicon Motion Systems, Oxford, UK) and exergame-related markerless motion capture using Kinect V2 (Microsoft Corporation, Redmond, WA, USA). Multimodal acquisition is coordinated through Vicon Nexus (V.2.16; Vicon Motion Systems, Oxford, UK), enabling time-synchronised recordings across all data streams.

The full experimental laboratory setup, including all sensor modalities, is illustrated in figure 1B. sEMG is used to record bilateral muscle activity from key postural and lower limb muscles, including the tibialis anterior, lateral gastrocnemius, soleus, gluteus medius, biceps femoris and erector spinae. Electrode placement follows SENIAM guidelines in combination with palpation.^49^ In seated reaching, only the erector spinae will be evaluated. IMUs are placed on the sternum, pelvis and non-paretic wrist. Additionally, during standing reaching and gait initiation, force plate data are collected with each foot placed on a separate force plate.

Tasks are executed according to a standardised protocol in terms of verbal instruction, trial sequence and rest intervals. The same setup and procedures are applied across all time points to ensure consistent longitudinal data.

The clinical assessments and PROMs, conducted without sensor instrumentation, include standardised tests to assess lower extremity function, trunk control, balance, gait capacity, functional independence, mental health and quality of life. In addition, daily physical activity will be monitored using an accelerometer (Activ8 Professional; 2M Engineering; The Netherlands), worn on the anterior upper leg for 72 consecutive hours at each assessment time point. The device may be worn on either the affected or unaffected side, as physical activity classification is not expected to differ meaningfully between sides.

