### Outcome measures

Outcome measures are collected at the entry visit and each applicable poststroke time point, according to the patient’s ability. Depending on functional ability, not all components may be feasible at early assessments. Participants who are not yet able to perform the exergame tasks will complete the feasible clinical assessments and PROMs only, and sensor-based exergame assessments will be added at later time points when they can be performed safely. For example, seated reaching may become feasible before standing reaching and gait initiation as motor ability improves. An overview of all outcome measures, including data sources, is provided in table 1.

**Table 1 T1:** Outcome measures, instruments and data sources

Outcome category	Outcome/variable	Data source
Patient characteristics		
	Sociodemographic profile (age, sex, occupation, ethnicity, education)	Medical record
	Stroke descriptors and relevant comorbidities (lesion side and site, type, aetiology, AF status/subtype)	Medical record
	Acute stroke severity	NIHSS
	Global cognition	MoCA
Sensor-based outcomes		
Exergame assessments	Postural control* (eg, postural sway)	IMUs; force plates
	Weight distribution*	Force plates
	Neuromuscular activity*	sEMG
	Movement coordination*	IMUs; Kinect; force plates
	Task accuracy (reach/step)	Kinect
	Upper-limb acceleration	IMUs
	Reaction and movement time	Kinect
Out-of-lab monitoring	Daily activity profile	Activ8 sensor
Clinical and patient-reported outcomes		
Clinical assessments	Lower-limb motor impairment	FM-LE (0–34); MI (0–100)
	Dynamic sitting balance	TIS (0–6)
	Standing balance	Mini-BEST (0–28) or BBS (0–56)
	Walking speed	10mWT (m/s)
	Ambulation category	FAC (0–5)
	Global disability	mRS (0–5)
PROMs	Anxiety and depression	HADS (0–21 subscores)
	Quality of life (health-related)	SF-36 (domain scores 0–100)

* Primary outcome domain. The four primary outcome domains are equally ranked, with no further hierarchy. All other outcome measures are secondary.

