#### Statistical analysis

For the primary objective, longitudinal change in outcomes representing the four primary sensor-based domains (postural control, weight distribution, movement coordination and neuromuscular activity) will be analysed using linear mixed-effects models. Secondary longitudinal analyses will apply the same modelling framework to task-performance measures, daily activity, clinical outcomes and PROMs. Baseline characteristics will be summarised descriptively. Feasibility and data availability will be reported per assessment timepoint, documenting (1) the proportion of participants completing each assessment, (2) the number of valid trials per condition for sensor-based tasks and (3) reasons for missing data at each timepoint.

To investigate longitudinal change, each outcome will be modelled as a function of Time (categorical: baseline, week 5, week 8, week 12 and week 24). Models will include subject-specific random intercepts to account for baseline differences between individuals. Where supported by convergence and reliable variance estimation, random slopes for Time will be added to capture heterogeneity in individual recovery trajectories.^67
68^ Estimated marginal means will be used to describe group-level recovery trajectories, and post hoc contrasts will quantify differences across the full study period and between assessment intervals. Within each outcome domain, multiplicity will be controlled using Holm-Bonferroni correction.

Individual predicted trajectories will be visualised by combining individual intercept and slope estimates with the fixed effects. These individual trajectories will be plotted alongside group-level trajectories to illustrate both average trends and the distribution of recovery profiles across participants. Standard diagnostic checks will be performed; if assumptions are violated, transformations or alternative model specifications will be considered.

To examine associations between sensor-derived metrics of movement quality and clinical outcome measures, a multivariate mixed-effects modelling approach will be used. First, separate linear mixed-effects models will be fitted for each individual outcome, using the same model structure described above for the longitudinal analyses. These models provide subject-specific random intercepts and, when supported by convergence, random slopes for Time, representing each participant’s baseline level and rate of change.

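### Sensor outcomes exist only for participants able to do the task at that visit, yet the model means are read as the group's recovery curve, so early means are likely too favourable and change may be biased

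*Protocol article*

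**What the plan says.** Under Eligibility criteria (text after Figure 1) the article states: "Independent walking, standing balance or the ability to perform the exergame tasks are not required for inclusion". Under Assessment protocol, "sensor-based exergame assessments are only performed when the participant is judged able to complete the respective task safely under supervision". Under Outcome measures, participants not yet able complete only what is feasible of the clinical tests and questionnaires, and "sensor-based exergame assessments will be added at later time points when they can be performed safely". The tasks open up in sequence: "seated reaching may become feasible before standing reaching and gait initiation as motor ability improves".

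These recordings carry the primary outcome. The Introduction says: "The primary objective is to characterise longitudinal change in sensor-derived postural control and movement quality", in four equally ranked domains, which Table 1 marks as primary.

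Under Statistical analysis, each outcome gets a linear mixed model with categorical Time (five levels), a random intercept and, where supported, random slopes. Then: "Estimated marginal means will be used to describe group-level recovery trajectories". The section also promises completion rates, valid trials and reasons for missing data per time point. It does not say whether the group is everyone enrolled, those ever able, or those able at each visit.

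**The concern.** Whether a primary value exists at a visit depends on the participant's motor ability at that visit, which is closely related to the postural control being measured. Early visits hold mainly the better performers, weaker participants join later, and those who never become able contribute nothing. A curve drawn from such data and labelled as the group's recovery would be read as the course of the enrolled cohort.

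Two things are at stake: the level of the curve, above all at early visits, and the change between visits, which is the primary objective. The recording rule is a safety rule and is not in question here; the issue is what the resulting means are said to describe.

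**Working it through.** **1. Which outcomes are exposed.** Table 1 gives force plates as the only source for weight distribution. Assessment protocol describes force-plate data only for standing reaching and gait initiation. In seated reaching, only one of the six named muscles, the erector spinae, is evaluated by sEMG. So one whole primary domain, and most of the neuromuscular one, exist only for participants who can stand or step, the tasks expected to become feasible later. Postural control and movement coordination also use IMUs and so have seated data.

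**2. What the mixed model does.** It uses all of a person's recorded visits, so someone first recorded at week 12 still informs the random intercept and, through it, the early means. That corrects part of the selection. It cannot correct for values missing because of the current unobserved state, nor represent people with no recording.

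**3. Size.** The plan has no figure to reproduce: it gives no share able, no SD and no expected change. Everything below is therefore assumed.

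- Outcome for person i at visit j: Y = b0 + b1·s + e, with s = ln(t/3)/ln(8) and t = 3, 5, 8, 12, 24 weeks. Hence s = 0 at entry and 1 at week 24.
- b0 has mean 0 and SD 1; b1 has mean 1 and SD 0.5; e has SD 0.5. True cohort entry mean is 0, true change 1.00.
- Correlation of b0 and b1: −0.6 (poorer starters gain more), 0, or 0.5 (poorer starters gain less).
- Y is recorded only if ability exceeds a cut-off of −0.5, 0 or 0.5, giving about 69%, 50% or 31% able at entry.
- Ability is either the current state b0 + b1·s, or a separate trait whose starting level correlates 0.5 with b0.
- 40,000 people; maximum-likelihood model with categorical Time, random intercept (RI) or intercept plus slope (RI+RS).

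Each cell gives results for 69% / 50% / 31% able at entry.

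| Ability | Gain in poorer starters | Change, RI | Change, RI+RS | Entry mean, RI | Entry mean, RI+RS |
|---|---|---|---|---|---|
| current state | more | 0.83 / 0.71 / 0.56 | 0.84 / 0.70 / 0.55 | 0.22 / 0.45 / 0.81 | 0.21 / 0.46 / 0.81 |
| current state | unrelated | 0.97 / 0.93 / 0.89 | 0.93 / 0.85 / 0.79 | 0.23 / 0.43 / 0.71 | 0.27 / 0.51 / 0.81 |
| current state | less | 1.08 / 1.11 / 1.16 | 1.01 / 1.01 / 1.00 | 0.24 / 0.41 / 0.61 | 0.30 / 0.51 / 0.76 |
| r = 0.5 | more | 0.92 / 0.88 / 0.83 | 0.94 / 0.91 / 0.87 | 0.13 / 0.21 / 0.33 | 0.11 / 0.18 / 0.29 |
| r = 0.5 | unrelated | 0.99 / 0.99 / 1.01 | 0.98 / 0.98 / 1.00 | 0.13 / 0.23 / 0.34 | 0.14 / 0.25 / 0.36 |
| r = 0.5 | less | 1.06 / 1.08 / 1.13 | 1.04 / 1.05 / 1.09 | 0.13 / 0.24 / 0.38 | 0.16 / 0.27 / 0.42 |

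**4. Reading it.** The entry mean is too high in every setting, by 0.11 to 0.81. The week-24 mean is also above the cohort's 1.00 (1.05 to 1.77), because 3% to 35% are never able. Change is the difference of two shifted means, so its error can go either way. With 31% able, ability following the current state and RI: 1.77 − 0.61 = 1.16 where poorer starters gain less, but 1.36 − 0.81, about 0.56 before rounding, where they gain more. The model does improve on the raw visit means, whose change was 0.22 to 0.94.

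A separate simulation with other assumed parameters (32% to 68% able at entry) put the entry mean 0.2 to 1.0 above the cohort's and change at 0.44 to 0.99 against about 1.0. Level bias is thus consistent across both exercises; the size and sign of the bias in change are not.

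**The case against.** The strongest reply has four parts.

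- **Ability is not movement quality.** The article's premise is that the two differ. If they are only loosely tied and gain is unrelated to start, the table shows change of 0.98 to 1.01, essentially unbiased. This stands for change; the entry mean is still 0.13 to 0.36 too high.
- **The selection is disclosed.** Availability and reasons are reported per visit, and the Discussion lists incomplete early sensor tasks as a limitation. True, but neither alters the estimate or qualifies the group label.
- **Missing-data assumptions may sit in an analysis plan not shown.** Their absence is not the finding. The point rests on two things the article does state, the recording rule and the interpretation of the means.
- **Seated reaching is feasible earlier.** It probably suffers less, but it yields no described force-plate data.

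A reader might go further and infer that the plan necessarily understates recovery. The documents do not support this: they do not say how gain relates to starting level, and change is overstated in most settings where poorer starters gain less. A reader might also infer that the means describe no definable group. Under missing at random they refer to participants with at least one recording, as if all could do the task at every visit; that group can be defined, but the article does not name it. Nor do the documents say that these means feed the virtual-twin models; they say only that the data may help inform future models.

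**Conclusion.** The point holds in this form. The contributing set changes by visit and task with an ability closely related to the outcome, and the mixed model reduces but does not remove that selection. Under the assumptions shown, early marginal means are too favourable for the enrolled cohort, by about 0.1 to 0.8 starting SDs at entry. Change from entry to week 24 may be biased, more often towards less change, with 0.55 to 1.16 found against a true 1.00. No single percentage can be attached to this trial. The size depends on the share able, how closely ability tracks the outcome and how gain relates to starting level, none of which is given. For people unable to do the task, the cohort value is itself hypothetical. Weight distribution and the other standing and stepping outcomes are most exposed.

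**What to change.** In Statistical analysis:

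1. State that sensor trajectories refer to participants able to perform the task, not to the enrolled cohort.
2. Report each contrast also in participants able at both visits compared, beside the proportions able, newly able and never able, by task. This is a clearly named group, not an estimate for the cohort: in the simulation, true change in those able at entry ran from 0.66 to 1.29.
3. Add a sensitivity analysis for ability-dependent missingness, for example a joint model with the FM-LE where it was recorded, building on the bivariate models already planned. In a simulation of 3,000 people with 35% to 50% able at entry, a joint fit with a clinical score available at every visit removed about 75% to 95% of the error in the visit means but not the error in change. It is a check, not a cure, and clinical tests are themselves done only where feasible.

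The cost is mainly wording and tables, since completion and reasons for missing data are already to be documented. The able-at-both contrasts use fewer participants and have wider intervals: with 100 enrolled and the assumed shares, a contrast from entry rests on at most about 31 to 69 people before dropout.
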